## Abstract

**Background:**

Fibromyalgia syndrome (FMS) is a complex chronic condition that makes high demands on patients’ self-management skills. Thus, patient education is considered an important component of multimodal therapy, although evidence regarding its effectiveness is scarce. The main objective of this study is to assess the effectiveness of an advanced self-management patient education program for patients with FMS as compared to usual care in the context of inpatient rehabilitation.

**Methods/Design:**

We conducted a multicenter cluster randomized controlled trial in 3 rehabilitation clinics. Clusters are groups of patients with FMS consecutively recruited within one week after admission. Patients of the intervention group receive the advanced multidisciplinary self-management patient education program (considering new knowledge on FMS, with a focus on transfer into everyday life), whereas patients in the control group receive standard patient education programs including information on FMS and coping with pain. A total of 566 patients are assessed at admission, at discharge and after 6 and 12 months, using patient reported questionnaires. Primary outcomes are patients’ disease- and treatment-specific knowledge at discharge and self-management skills after 6 months. Secondary outcomes include satisfaction, attitudes and coping competences, health-promoting behavior, psychological distress, health impairment and participation. Treatment effects between groups are evaluated using multilevel regression analysis adjusting for baseline values.

**Discussion:**

The study evaluates the effectiveness of a self-management patient education program for patients with FMS in the context of inpatient rehabilitation in a cluster randomized trial. Study results will show whether self-management patient education is beneficial for this group of patients.

**Trial registration:**

German Clinical Trials Register, DRKS00008782, Registered 8 July 2015

## Background

This is a study protocol of a cluster randomized trial based on CONSORT and SPIRIT recommendations [1, 2].

The fibromyalgia syndrome (FMS) is characterized by chronic widespread pain and additional symptoms as fatigue, unrefreshed sleep, cognitive symptoms and various somatic symptoms [3]. About 2–7 % of the general population are affected by FMS, with a higher prevalence in women [4–6]. The disorder causes substantial burden for the individual [7] and high socioeconomic costs through increased healthcare utilization [8]. A study of a German health insurance company estimated total yearly costs to 4.331 €, thereof 3602 € direct costs [9]. Another study calculated adjusted yearly direct costs of $2417 and indirect costs of $10.001 in Germany [10]. In an US-sample, mean healthcare costs for FMS patients were three times higher than for other patients [11]. According to FMS guidelines [12–14], treatment should be multidisciplinary and combine different pharmacologic and non-pharmacologic therapies, with self-management patient education as one recommended component. Research indicates that multicomponent therapy including psychological and exercise therapy has positive effects on key symptoms of FMS, self-efficacy and physical fitness [15]. Information about the relative effectiveness of different treatment components is scarce [16]. Meta-analytical results show small but robust positive effects of psychological treatments (including patient education) for fibromyalgia [17]. There is limited evidence regarding the effectiveness of self-management patient education for patients with FMS. Comparison of studies is difficult because of different contents and formats of education programs and evaluation of multimodal programs with different components [18–33]. Moreover, many studies use some form of education as control (not as intervention) condition or do not assess long-term effectiveness of self-management education [34]. Further research is needed to determine the independent effects of patient education [35].

An existing German patient education program for patients with FMS in the medical rehabilitation system [36] proved its worth over years, but there was a need to revise it. It did not consider up-to-date knowledge about FMS, especially the new national guideline [12], had potential for didactical improvements and should be advanced with regard to patients’ needs [37]. Furthermore, its effectiveness has not been evaluated so far. Therefore, based on this program, an advanced self-management patient education program was developed. This new interactive, didactically revised program aims to promote a biopsychosocial understanding and self-management of the disease. It considers current knowledge on FMS and is consistent with the current national guideline [12]. It has a focus on the transfer of pain and stress management and physical activity into everyday life. Although content and structure are similar to the prior program, it includes more practical exercises and emphasizes transfer into everyday life through action planning.

The objective of this cluster randomized controlled study is to evaluate this advanced self-management patient education program for patients with fibromyalgia syndrome [38] in inpatient rehabilitation. The main research questions are the short-, intermediate- and long-term effectiveness of the self-management program compared to usual care, in this case an active control (standard patient education programs). We hypothesize that the program is superior to usual care regarding both disease- and treatment-specific knowledge at discharge of rehabilitation and self-management competence 6 months after rehabilitation (primary outcomes). Additionally, we expect superior effectiveness regarding satisfaction with the program, attitudes towards the illness and coping competences, health-promoting behavior, psychological distress, health impairment and participation (secondary outcomes). The role of potential moderator variables (e.g. age, psychological co-morbidity, duration of disease) is examined in an exploratory manner.

## Methods/Design

### Study design and data collection

This study is a multicenter cluster randomized controlled trial (RCT) conducted in three German inpatient rehabilitation clinics. Clusters are groups of patients with FMS consecutively recruited within one week after admission to the clinic. The superiority trial has two arms. Patients of the intervention group (IG) receive the advanced self-management patient education program. Patients of the control group (CG) receive standard patient education programs including information on FMS and coping with pain (usual care). Data are collected at admission (t1), discharge (t2) and after 6 (t3) and 12 months (t4) with standardized and self-developed patient-reported questionnaires. Additionally, medical data are collected during rehabilitation. Cluster randomization was chosen for practical reasons (to have groups that are sufficiently large), for blinding patients as to intervention conditions and to prevent contamination between interventions. Clusters of patients are randomly assigned to the two intervention conditions in a 1:1 ratio. For t1 and t2, patients receive the questionnaire in the inpatient rehabilitation clinic. For t3 and t4, patients receive the questionnaire by mail and are reminded with a second letter if necessary. Figure 1 shows the study protocol diagram.

**Fig. 1 Fig1:**
[figure not shown]
Study protocol diagram of data collection process

### Ethical aspects

This study conforms to the principles of the Declaration of Helsinki. It was approved by the Ethics Committee of the Faculty of Medicine, University of Würzburg, on April 22, 2014 (reference number: 46/14). Participants are informed about the study in the initial consultation and additionally are provided an information sheet. Participation is voluntary and based on written informed consent. Patients are informed about their right to refuse participation in the study or withdraw consent to participate without consequences for their treatment. They are also informed about data protection through collecting data using code numbers for each patient.

### Participants

Considered for inclusion are adult patients in inpatient rehabilitation clinics with the main diagnosis fibromyalgia syndrome (ICD-10: M79.7). Exclusion criteria are insufficient German language ability, severe psychiatric comorbidity which leads to inability to participate in an educational group, cognitive impairment or not corrected severe visual or hearing impairment. Patients with FMS are admitted to the clinics every two weeks. All patients admitted during this period of one week are eligible to build a cluster, with a minimum of 3 participants per group.

### Intervention

Inpatient rehabilitation in Germany for patients with FMS is multimodal and includes medical treatment, exercise therapy, health education, psychological support, relaxation and social counseling over a period of three (for severe cases sometimes four) weeks. This trial compares a self-management patient education group program to standard patient education programs (usual care), both within inpatient rheumatological rehabilitation centers.

Intervention group (IG). Participants in the intervention group attend a disease-specific self-management patient education program ([38], see Table 1). It consists of 6 sessions of 90 min each and one (optional) preparing session, all delivered in small groups (12 participants maximum) of closed format. The program is manual-based and led by physicians, psychologists and physiotherapists, respectively. Methods are interactive, with patients actively involved and different didactic methods used (interactive short lectures, group discussion, practice, individual work). Materials include presentations, flipchart, work sheets and patient information sheets. Contents of the sessions include fibromyalgia-related information (e.g. symptoms, diagnosis, course of disease, causes and influencing factors, frequency), information about treatment (e.g. treatment options, medication, physical therapy, psychotherapy, risks and benefits of alternative therapies), coping with pain and stress as well as promotion of sustained physical activity. There is a focus on both self-management and transfer into everyday life through action planning. Evaluations by patients performed during formative evaluation showed a high satisfaction with the program [38]. All trainers are experienced with patients with FMS. Additionally, the trainers receive a 1.5 day train-the-trainer course held by project staff and a psychologist with experience in FMS-education.

**Table 1 Tab1:** Structure of the advanced self-management patient education program for patients with fibromyalgia syndrome

Session		Trainer
0	Introduction, questions and expectations (optional)	Psychologist
1	The fibromyalgia syndrome – What does that mean? (symptoms, diagnosis, course, causes and influencing factors, frequency, communication with health professionals)	Physician
2	How is the fibromyalgia syndrome treated? (treatment options, medication, physical therapy, psychotherapy, risks and benefits of alternative therapies)	Physician
3	Dealing with pain (acute vs. chronic pain, development and sustainment of pain, consequences, relationships to depression and anxiety, coping with pain)	Psychologist
4	Everything hurts! – Thus, why moving? (possibilities of physical activity, consequences, physical exercises, important principals of training, action and coping planning)	Physiotherapist
5	Everything grows over my head! – Ways out of stress (types of stressors, development of stress, stress reaction and consequences, relationship to pain, coping with stress, exercises)	Psychologist
6	Managing daily life (explaining the condition to others, goals for daily life, checking the action plans, improving sleep quality, personal conclusion)	Psychologist

Control group (CG). Control condition is the treatment as usual including education as delivered in the respective clinic. In one cooperating clinic, usual care is the previously practiced, interactive patient education for fibromyalgia syndrome with 5 sessions (90 min each; content: illness and treatment information, coping with pain and stress, exercise therapy). Trainers are a psychologist, a physician, a physiotherapist and an occupational therapist or nutritionist. In the second cooperating clinic, patients participate in a coping with pain group with 4 sessions (90 min each; content: information about pain, coping with pain, transfer into daily life) led by a psychologist, physiotherapist and physician and receive a flyer about the fibromyalgia syndrome. In the third cooperating clinic, patients are informed by 3 physician-delivered lectures (60 min each) about chronic pain, fibromyalgia syndrome and stress and may participate in educational group programs for pain or stress coping (each with 4 sessions of 45 min each, led by psychologists) or autogenic training, as indicated. There are differences between the three control conditions, but they also have common characteristics. They all include information about FMS and coping with pain. In contrast to the intervention condition, control conditions do not explicitly consider the up-to-date knowledge about FMS, the new guideline [12] and newly recorded needs of patients with FMS [38]. They are partly less interactive and less self-management-oriented as they do not include action and coping planning and do not have such a strong emphasis on transfer into everyday life.

### Outcomes and Measures

In this study, the effects of the treatment conditions are assessed at the individual level using patient-reported outcomes. Different proximal and distal outcomes at different measurement points are used for evaluation [39]. The primary outcome is disease- and treatment-specific knowledge at discharge of inpatient rehabilitation and patients’ subjective self-management competence 6 months after rehabilitation. Secondary outcomes include treatment satisfaction, attitudes towards the illness and coping competences, health-promoting behavior, psychological distress, health impairment and participation. For measuring knowledge, a new measure was developed based on the content of the patient education program (the same information is also given in the control condition). Acceptance of the disease and communication about the disease with others are also measured with a self-developed questionnaire. Both were pre-tested in a sample of n = 91 patients with fibromyalgia, items were selected due to difficulty and comprehensibility (knowledge) or results from factor analysis (acceptance and communication). The other outcomes are assessed by standardized, validated measures. Detailed information concerning the outcomes and questionnaires are shown in Table 2. It will take about 45 min for the patient to fill out the questionnaires at each measurement point.

**Table 2 Tab2:** Outcomes, measures, assessment

Outcome	Measure	Assessment			
		t1	t2	t3	t4
*Primary outcomes*					
Disease- and treatment-specific knowledge	Self-developed questionnaire	x	x	-	x
Subjective self-management competence	Health education impact questionnaire heiQ, German version [40], subscales Skill and technique acquisition, Self-monitoring and insight	x	x	x	x
*Secondary outcomes*					
Treatment satisfaction	Patient education satisfaction questionnaire [45]	-	x	x	x
Attitudes and coping competences:					
Pain-related controllability	Rheumatology Attitudes Index, German version [46]	x	x	x	x
Acceptance of the disease and communication with others	Self-developed questionnaire	x	x	x	x
Behavior determinants for physical activity and relaxation	HAPA-scales [47, 48]	x	x	-	-
Behavior:					
Health-promoting behavior, active lifestyle	Godin Leisure-Time Exercise Questionnaire [49], German modified version	x	-	x	x
	Relaxation index [50]	x	-	x	x
	Health education impact questionnaire heiQ, German version, subscales Active engagement in life, Health-promoting activities	x	-	x	x
Interaction in the health system	Health education impact questionnaire heiQ, German version, subscale Health service navigation	x	-	x	x
Health impairment	Fibromyalgia Impact Questionnaire German version, without the physical functioning subscale, FIQ-G [51, 52]	x	x	x	x
Psychological distress	Short form of the Patient Health Questionnaire PHQ-4 [53]	x	x	x	x
Participation	Fibromyalgia Participation Questionnaire FPQ [54]	x	-	x	x

Additionally, potential moderator variables as sociodemographic parameters, duration of disease and social support (subscale social integration and support of the Health Education Impact Questionnaire heiQ [40]) are assessed as reported by the patients. Medical data as diagnoses, medication, ACR-criteria (diagnostic criteria of the American College of Rheumatology [3]) or working ability are provided by the attending physicians.

### Sample size

The needed sample size was calculated based on expected effect size, power and design effect (intracluster correlation, expected average cluster size, [41]). This calculation comprises some uncertainties as size of ICC, actual cluster size, effect sizes and dropout rates. There are no previous studies in similar contexts with similar interventions and outcomes which enable exact estimations. We assumed small to medium effects (*d* = 0.3) in the primary outcome due to the comparison with a control group that also gets a comprehensive treatment. Thus, setting alpha risk to 0.05 and power to 0.8, a sample of 175 per group is needed for two-tailed tests. Assuming an intraclass correlation coefficient (ICC) of 0.01 and an average cluster size of 6, the resulting design effect is 1.05, resulting in a needed sample size of 184 per group. Thus, 566 participants have to be recruited, based on an estimated maximum dropout rate of 35 % during follow-up. Because power to detect smaller effects between groups may be too low, effect sizes will be reported.

### Randomization, allocation concealment and blinding

External cluster-randomization is performed by the research institute (central randomization) using a computer-generated list of random numbers, ensuring a 1:1 ratio for both treatment conditions. FMS patients are recruited at admission to inpatient rehabilitation by study assistants in the clinics and allocated to the next education group (cluster). A new treatment condition starts every two weeks. Allocation concealment will be attained by providing information about allocation (by telephone or email) only after a cluster has been recruited. Patients are blinded regarding the allocated study arm. It is not possible to blind staff in the rehabilitation clinics, especially those performing the educational interventions.

### Statistical methods

All analyses are performed with SPSS for Windows. After exploration of missing patterns, missing data in accordance with missing at random assumptions will be imputed by a multiple imputation procedure. T-tests for independent variables are used for nonresponder- and dropout-analyses. The evaluation of primary and secondary endpoints is carried out according to the intention-to-treat-principle. Before analyzing the combined data of the three clinics we will confirm that 'clinic' is not a moderator variable. Treatment effects between groups will be evaluated separately for each follow-up time point using multilevel regression analysis adjusting for baseline values [41–43]. Treatment group is included in the models as fixed effect and individuals are nested in clusters (education groups) as random effects. Report of outcomes includes ICCs, statistical significance (*p* < 0.05, 2-sided) and effect sizes [44] for differences between groups. For exploratory moderator analyses, potential moderator variables are included as an additional fixed factor or covariate, respectively.

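### Pooling is made conditional on confirming that clinic is not a moderator, which a trial sized only for the pooled effect cannot confirm

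*Protocol article*

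**What the plan says.** The Statistical methods section of the protocol article sets a condition on the main analysis: "Before analyzing the combined data of the three clinics we will confirm that 'clinic' is not a moderator variable". The treatment effect is then estimated by multilevel regression adjusted for baseline, with treatment as a fixed effect and education groups as random effects.

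The Sample size section plans for the pooled comparison only. It states "We assumed small to medium effects (*d* = 0.3) in the primary outcome" and continues: "setting alpha risk to 0.05 and power to 0.8, a sample of 175 per group is needed for two-tailed tests". Clustering is then allowed for: "Assuming an intraclass correlation coefficient (ICC) of 0.01 and an average cluster size of 6", and "the resulting design effect is 1.05, resulting in a needed sample size of 184 per group". Allowing for a maximum dropout of 35% during follow-up brings the recruitment target to 566.

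The trial is "conducted in three German inpatient rehabilitation clinics", and usual care is not the same in each. Under Intervention, the control is the clinic's previous interactive fibromyalgia program (five 90-minute sessions) in one clinic. In the second it is a pain-coping group (four 90-minute sessions) plus a flyer. In the third it is three 60-minute lectures with further groups as indicated. The article acknowledges this: "There are differences between the three control conditions, but they also have common characteristics". Of the new program, the Background says: "Although content and structure are similar to the prior program".

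**The concern.** The condition asks the trial to establish a null hypothesis before it may carry out the analysis it was sized for. Failing to find an interaction is not evidence that there is none unless the estimate is precise enough to exclude differences that matter, and nothing in the sample size addresses that.

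The condition can go wrong in two ways. If effects differ between clinics, a low-powered check may well be passed, and a non-significant test may then be read as showing a uniform effect. If effects do not differ, a chance significant interaction would block the only comparison the trial is powered for.

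Different effects are plausible here. In one clinic the new program is compared with an earlier multi-session fibromyalgia program, in another mainly with lectures.

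**Working it through.** **1. The plan's own figure.** For d = 0.3, two-sided alpha 0.05 and power 0.80, the normal formula gives 2 × ((1.960 + 0.842)/0.3)² = 174.4, so 175 per group. The design effect is 1 + (6 − 1) × 0.01 = 1.05, and 175 × 1.05 = 183.75, so 184 per group or 368 in total. Then 368/(1 − 0.35) = 566.2. The stated 175, 184 and 566 are reproduced.

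**2. Inputs for the clinic check.** From the article: three clinics, 1:1 allocation, design effect 1.05, and 368 evaluable or 566 recruited. Assumed, because the article does not give them: equal thirds per clinic, a 5% Wald test on 2 degrees of freedom, and a share R² of outcome variance explained by baseline of 0 to 0.5. The outcome SD is 1. The figure of 566 analysed is an upper bound.

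**3. Precision.** The variance of one clinic's treatment effect is v = 4 × 1.05 × (1 − R²)/(N/3). At N = 368 and R² = 0 this is 4.2/122.7 = 0.0342, so SE = 0.185. The SE of a difference between two clinics is √(2 × 0.0342) = 0.262, and the 95% half-width is 1.96 × 0.262 = 0.51 SD, against an assumed effect of 0.3.

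**4. Power of the interaction test.** The noncentrality is Σ(dᵢ − mean)²/v. For true effects 0.1, 0.3 and 0.5 the sum of squares is 0.04 + 0 + 0.04 = 0.08. At N = 368 and R² = 0, 0.08/0.0342 = 2.34, and the noncentral chi-square gives power 0.26.

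**5. Showing that the effects are similar.** Confirming similarity needs an equivalence argument. With two one-sided 5% tests and a margin of 0.3 SD (an illustrative margin equal to the assumed effect), power is max(0, 2Φ(0.3/SE − 1.645) − 1), where SE is that of the difference.

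| N analysed | R² | Power, 0.1/0.3/0.5 | 95% half-width, two-clinic difference | Power to show difference below 0.3 SD |
|---|---|---|---|---|
| 368 | 0 | 0.26 | 0.51 | 0 |
| 368 | 0.25 | 0.33 | 0.44 | 0 |
| 368 | 0.5 | 0.48 | 0.36 | 0 |
| 566 | 0 | 0.38 | 0.41 | 0 |
| 566 | 0.25 | 0.49 | 0.36 | 0 |
| 566 | 0.5 | 0.67 | 0.29 | 0.29 |

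The check would therefore be passed despite this pattern 52% to 74% of the time at 368 analysed, and 33% to 62% at 566. For 0, 0.3 and 0.6 (no effect in one clinic, twice the assumed effect in another), power at 368 is 0.53 with R² = 0 and 0.84 with R² = 0.5.

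**6. Cost when there is no moderation.** A 5% test blocks pooling 5% of the time per outcome. Over the two primary outcomes this is 1 − 0.95² = 0.0975, about 10%, if the tests are independent. The probability of both passing the check and finding d = 0.3 is about 0.95 × 0.80 = 0.76 instead of 0.80. A single clinic analysed alone has power of about 0.37 for d = 0.3.

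**The case against.** Several stronger readings are tempting, and the documents do not support them.

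- **That the check cannot be done with three clinics.** It can. At 368 analysed and R² = 0, an evenly spaced spread of about 0.81 SD across clinics would be detected with 80% power, and strong baseline adjustment lowers that. What limits it is about 123 evaluable patients per clinic, not the number of clinics.
- **That testing first distorts the pooled inference.** This is not shown. With equal clinics the heterogeneity statistic is independent of the pooled estimate. In a simulation of 1,000,000 trials (368 analysed, R² = 0), those that passed the check had a pooled type I error of 0.050, power of 0.80 and a mean estimate of 0.300 when the true effect was 0.3.
- **That moderation is likely.** The article does not quantify it. It says that all three controls cover fibromyalgia information and coping with pain and, under Outcomes and Measures, that control patients receive the same information on which the knowledge questionnaire is based. Some variation is plausible; no more can be said.
- **That about 14% of trials would be blocked by chance.** That figure comes from counting three independent comparisons, 1 − 0.95³. Two of the three would be subscales of one questionnaire in the same patients, so independence is doubtful.
- **That a fallback is missing.** A condensed article may leave the test, its threshold and what follows a failed check to a fuller document. No weight is put on their absence.

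It is also fair to say that 368 need not apply to knowledge, which is measured at discharge, because the 35% is a maximum over follow-up. That is why the range up to 566 is shown. The article is open about the differences between controls and promises effect sizes. None of this rescues the condition itself: a fuller plan could specify the test, but it could not make a non-significant result confirm the absence of moderation at this sample size.

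**Conclusion.** The point stands as a flaw in the stated rule and should be fixed. The combined analysis depends on a confirmation that the design cannot give. A moderate spread of 0.1, 0.3 and 0.5 SD would be missed between one third and three quarters of the time across the range examined. The interval for a difference between two clinics reaches at best ±0.29 SD. In the other direction, the rule costs about 5% per outcome of otherwise sound pooled analyses.

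The figures rest on equal clinics, a 5% test on 2 degrees of freedom and baseline R² between 0 and 0.5, none of which the article states for this check. The design effect of 1.05 and the sample sizes are the article's own. The conclusion does not extend to the validity of the pooled test once reached, nor to any claim that the effect does differ by clinic.

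**What to change.** Delete the precondition. State that the combined analysis, with clinic added to the multilevel model as a fixed effect, is the primary analysis in all cases. Report the clinic-by-treatment interaction and the three clinic-specific effects with 95% confidence intervals as a planned description of heterogeneity, interpreted against what each clinic's control program contains, and say that a non-significant interaction will not be taken as evidence of a uniform effect.

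The cost is one rewritten sentence under Statistical methods and one additional results table. No further patients or data are needed.

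### The multilevel model has no clinic term, so clinic differences not carried by baseline go into the education-group variance and cost precision

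*Protocol article*

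**What the plan says.** The design is a "multicenter cluster randomized controlled trial (RCT) conducted in three German inpatient rehabilitation clinics" (Study design and data collection). Patients sit in education groups, and education groups sit in clinics.

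The Statistical methods section says effects are estimated separately at each time point "using multilevel regression analysis adjusting for baseline values". It then gives the structure: "Treatment group is included in the models as fixed effect and individuals are nested in clusters (education groups) as random effects". ICCs are to be reported. Clinic has one stated role: "Before analyzing the combined data of the three clinics we will confirm that 'clinic' is not a moderator variable".

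On usual care, the Intervention section concedes: "There are differences between the three control conditions, but they also have common characteristics". It describes five 90-minute interactive sessions in one clinic, four 90-minute pain-coping sessions plus a flyer in another, and three 60-minute lectures with optional groups in the third.

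Allocation is described as "using a computer-generated list of random numbers, ensuring a 1:1 ratio for both treatment conditions"; the article does not say whether the list was run by clinic. The sample size rests on "Assuming an intraclass correlation coefficient (ICC) of 0.01 and an average cluster size of 6".

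**The concern.** The data have three levels and the stated model represents two. All education groups are treated as exchangeable draws around one mean per arm, whichever clinic they come from. If clinics differ in outcome after baseline adjustment, three things follow.

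- The difference is counted as variance between education groups. The reported ICC then mixes clinic and group variance and is not comparable with the planned 0.01.
- If the clinic mix differs between arms by chance, the treatment estimate carries that noise.
- If the clinic mix is balanced by design, the model's standard error still includes clinic variance that has cancelled out of the estimate, so the test is conservative.

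The moderator check does not help. Absence of interaction is compatible with large clinic main effects, and the pooled analysis that follows still omits them. Baseline adjustment helps only in part, because differences produced by the clinic's own programme arise after t1. For treatment satisfaction it cannot help at all, since Table 2 shows no t1 value.

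The planning ICC of 0.01 leaves little room for this extra variance.

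**Working it through.** **Inputs.** From Sample size: d = 0.3, two-sided alpha 0.05, power 0.80, ICC 0.01, group size 6, dropout 35 %, 566 recruited. Assumed, because the documents give no figure: a between-clinic SD s, after baseline adjustment, of 0.10 to 0.30 residual SD.

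**1. The plan's own figures.** n = 2 × (1.96 + 0.8416)² / 0.3² = 174.4, so 175 per arm. Design effect = 1 + 5 × 0.01 = 1.05; 175 × 1.05 = 183.75, so 184. 368 / 0.65 = 566.2, against 566 stated. The figures reproduce, with no gain from a baseline covariate included. Power = Φ(0.3 × √(184 / (2 × 1.05)) − 1.96) = 0.80.

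**2. Group size.** 566 / 6 gives about 94 groups as recruited, but 184 per arm is the number after dropout. If 368 patients remain in 94 groups, 368 / 94 = 3.9 are analysed per group. If 6 is the analysed size, there are 368 / 6 ≈ 61 groups. Both cases are shown.

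**3. Power without a clinic term.** Apparent ICC = (0.01 + s²) / (1 + s²); design effect DE = 1 + (m − 1) × ICC; power = Φ(0.3 × √(184 / (2 × DE)) − 1.96).

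Example, s = 0.20 and m = 6: ICC = 0.05 / 1.04 = 0.048; DE = 1.24; 184 / 1.24 = 148; power = Φ(0.62) = 0.73.

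| Clinic SD | Apparent ICC | DE, m = 6 | Power, m = 6 | Power, m = 3.9 |
|---|---|---|---|---|
| 0 | 0.010 | 1.05 | 0.80 | 0.81 |
| 0.10 | 0.020 | 1.10 | 0.78 | 0.80 |
| 0.15 | 0.032 | 1.16 | 0.76 | 0.79 |
| 0.20 | 0.048 | 1.24 | 0.73 | 0.77 |
| 0.30 | 0.092 | 1.46 | 0.66 | 0.72 |

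**4. With and without clinic, m = 6.** Let r be the clinic share of total variance, with total SD 1. Without clinic, ICC = 0.01 + r. With a clinic fixed effect, the SD is √(1 − r) and the ICC is 0.01 / (1 − r).

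| r | Power without | Power with |
|---|---|---|
| 1 % | 0.78 | 0.81 |
| 2 % | 0.77 | 0.81 |
| 5 % | 0.71 | 0.82 |
| 10 % | 0.64 | 0.84 |

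**5. Simulation of the test.** Settings: 60 groups of 6, three equal clinics, 6,000 runs each, regression on group means, no baseline covariate.

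| r | Allocation | Type I error without / with clinic | Power without / with clinic |
|---|---|---|---|
| 0 | not by clinic | 0.053 / 0.054 | 0.785 / 0.773 |
| 5 % | not by clinic | 0.049 / 0.046 | 0.68 / 0.78 |
| 5 % | balanced by clinic | 0.023 / 0.045 | 0.71 / 0.80 |

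**6. Chance imbalance.** If 94 groups from three near-equal clinics are allocated without regard to clinic (20,000 simulated allocations), a clinic's share differs between arms with SD about 10 percentage points. With a clinic SD of 0.22 (r about 5 %), the resulting shift in the treatment estimate has SD 0.046 and exceeds 0.086 in absolute value in 5 % of allocations. The target is d = 0.3.

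**7. Allowing for baseline adjustment.** Suppose the baseline-outcome correlation is ρ (assumed) and d is divided by √(1 − ρ²). At m = 6, power for the four clinic SDs in step 3 becomes 0.85 / 0.83 / 0.80 / 0.74 at ρ = 0.4 and 0.89 / 0.87 / 0.85 / 0.79 at ρ = 0.5.

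**The case against.** **The article is condensed.** Two sentences on the model need not be a complete covariate list, and stratification is often stated only in the full protocol. This stands for randomisation: the article does not say the list ignored clinic, and nothing here relies on that. It has less force for the model, whose fixed and random terms are given, with clinic assigned a different role.

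**The cited clinic differences lie in the control arm.** They point mainly to interaction, which the moderator check targets. This is partly right. But if control means differ by δ between two clinics and intervention means do not, the two-arm averages still differ by δ / 2, which is a clinic main effect. If the moderator check detects nothing, that part stays in the error.

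**The moderator analysis would itself contain clinic.** Probably so, since the article enters moderators as fixed factors or covariates in its exploratory analyses. That does not carry clinic into the primary model.

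**Baseline adjustment already does much of the work, and the power loss depends on invented SDs.** Both points stand. Both primary outcomes have t1 values, and step 7 shows that a moderate baseline correlation can keep power near or above 0.80 in most scenarios. In addition, 35 % is a maximum dropout over follow-up, so knowledge at discharge will probably be analysed in more than 184 per arm.

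**A reader might infer that ignoring clinic makes the inference anti-conservative or biases the effect.** The documents do not support this. Treatment is randomised by group, and the simulated type I error is about 0.05 or, with balance by clinic, about 0.02.

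**Conclusion.** The point holds as a matter of efficiency. The stated model omits clinic, and the moderator check does not replace it. Residual clinic differences, and all clinic differences for treatment satisfaction, go into the group variance and the reported ICC.

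The size rests on an assumed clinic SD of 0.10 to 0.30 residual SD. Planned power falls to 0.78–0.66 with 6 analysed per group, or 0.80–0.72 with 3.9, before any baseline gain. At the lower end the loss is slight.

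Two stronger readings should be avoided. One is that the trial is underpowered; the between-clinic variance and the baseline correlation are both unknown, so this cannot be said. The other is that allocation was unbalanced by clinic; the article is silent on it. The recommendation does not depend on which applies: when clinics differ, the clinic term improves power under either form of allocation.

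**What to change.** Include clinic as a fixed effect (two indicator variables) in every primary and secondary multilevel model, alongside treatment and, where one exists, the baseline value. Keep education group within clinic as the random effect; three clinics are too few to estimate a clinic variance as a random effect. Report the ICC conditional on clinic so that it can be set against the planned 0.01. State whether the randomisation list was run by clinic, so that readers can judge the balance.

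The cost is two degrees of freedom and a phrase in the methods. Clinic is known for every patient, so no new data are needed. If clinics do not differ at all, the simulated price is about 0.01 of power (0.785 against 0.773, allocation not by clinic).
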